#### Efficacy.

Improvement in limb perfusion [34]: Assessed by thermography [35,36] (significant increase in limb temperature > 0.3 ºC), vascular ultrasound with Doppler (flow wave characteristics and flow velocity incrementation), ABI [29,30] (increase in ABI value ≥ 0.15 for participants with ABI < 0.9), transcutaneous capnography [37] (incrementation ≥ 10% in O_2_ levels and/or decrease ≤ 10% in CO_2_ levels measured at the base of the hallux and the ankle, behind the medial malleolus) and WIfI (the Society for Vascular Surgery Lower Extremity Threatened Limb Classification System: risk stratification based on wound, ischemia, and foot infection) [38,39].Improvement in quality of life: assessed by the SF-36 scale (Medical Outcomes Study 36 – Item Short-Form Health Survey) [40].Reduction in pain: Assessed by the Visual Analogue Scale (VAS) [41] and reduction in the use of analgesics (quantitatively and qualitatively).Partial ulcer healing: Assessed by measuring epithelialization of the ulcer. The total ulcer area will be analyzed using the area measurement tool in the free software ImageJ™ [42,43].Improvement in health perception: Assessed by the EQ-5D scale by EuroQol Group [44].Clinical improvement: Observed through physiological (blood pressure) and laboratory parameters (glycemia, glycated hemoglobin, HDL, LDL, total cholesterol, triglycerides, leukogram, hematocrit, uric acid, urea, creatinine, CRP, sodium, potassium, alkaline phosphatase (ALP), alanine transaminase (ALT), aspartate transferase (AST), gamma-glutamyl transferase (GGT), bilirubin, total protein, albumin, prothrombin time (PT), partial thromboplastin time (PTT)).Formation of granulation tissue in the ulcer.Changes in the systemic inflammatory profile with a predominantly cellular immune response through analysis of immunomodulatory cytokines (Th1, Th2, and Th17) [45,46].

### 
Participant timeline

Follow-up of patients will continue for 120 days from the moment they receive treatment with the proposed advanced cell therapy. Time required for screening and preparations will not count toward the study follow-up period. Participants will be reassessed on days 7, 30, 60, 90, and 120 days after randomization. The closing assessment will be carried out after 120 days (assessment 6). After completing their participation in the study, the participants will be referred for routine follow-up at the vascular surgery outpatient clinic of the Clinical Hospital of the Faculty of Medicine of Botucatu. During this period, extra visits may occur, if necessary (S3 File Table 1 Assessment Schedule).

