### Sample size

The sample calculation considered two independent samples with an estimated proportion of the ulcer healing rate of 75% for group 1, which will be treated with cell therapy, and 30% for group 2, which will be treated with hydrogel dressing. Assuming a test power of 80% and a significance level of 5% for a two-sided test, the sample was defined as 20 participants for group 1 and 20 participants for group 2 (1:1 allocation). This study was designed to be analyzed with intention to treat (ITT).

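### The CO2 limb of the capnography criterion sets 10% as a ceiling on the fall, so small falls count as improvement and large ones do not

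*Protocol article*

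**What the plan says.** The criterion is in the protocol article, Secondary outcomes, Efficacy, in the item on limb perfusion. For transcutaneous capnography it reads "incrementation ≥ 10% in O_2_ levels and/or", followed directly by "decrease ≤ 10% in CO_2_ levels measured at the base of the hallux", with the ankle as a second site.

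The same sentence sets two other numeric thresholds for perfusion:

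- thermography: "significant increase in limb temperature > 0.3 ºC"
- ankle-brachial index: "increase in ABI value ≥ 0.15 for participants with ABI < 0.9"

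Doppler ultrasound and WIfI are also listed, without a numeric cut-off. No other section of the article restates or corrects the CO2 threshold.

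**The concern.** The word for a decrease already gives the direction of change, so an upper bound of 10% limits how large the fall may be. The rule then accepts falls that could be measurement noise and leaves out the falls that would suggest better perfusion. The connective matters too: with and/or, meeting the CO2 limb is enough, so the O2 limb cannot screen out someone who qualifies on a trivial CO2 change.

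At stake is any classification of participants as improved on capnography. Under the written rule it would be diluted by noise. If the intended direction is settled only once data are in hand, a prespecified threshold becomes a post hoc choice in an open-label trial.

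**Working it through.** The threshold is a definition, so the plan has no calculated figure to reproduce. The check has three parts.

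**1. The thresholds side by side (all from Secondary outcomes, Efficacy).**

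| Measure | Direction of improvement | Threshold as written | Type |
|---|---|---|---|
| Limb temperature | rise | > 0.3 ºC | minimum |
| ABI | rise | ≥ 0.15 | minimum |
| O2 | rise | ≥ 10% | minimum |
| CO2 | fall | ≤ 10% | maximum |

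Only the CO2 limb is a maximum.

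**2. Which falls qualify.** Let *d* be the percent fall in CO2. The written limb is 0 < *d* ≤ 10; the mirror of the O2 limb is *d* ≥ 10, the same as a signed change ≤ -10%.

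| Fall *d* | Written limb | Mirror of O2 limb |
|---|---|---|
| 1%, 5%, 9.9% | improved | not improved |
| 10% | improved | improved |
| 10.1%, 15%, 20%, 30% | not improved | improved |

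For falls, the two rules agree only at exactly 10%. This result needs no distributional assumption.

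**3. Illustration of size, CO2 limb only.** Assumptions, none of them from the document: one CO2 change per participant, with *d* normal, mean μ and SD σ. I use σ = 10%, with a range of 5% to 15%.

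- Written limb: P = Φ((10 − μ)/σ) − Φ((0 − μ)/σ)
- Mirror limb: P = 1 − Φ((10 − μ)/σ)

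At σ = 10:

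- No true change (μ = 0), written: Φ(1) − Φ(0) = 0.841 − 0.500 = 0.341
- True mean fall of 20% (μ = 20), written: Φ(−1) − Φ(−2) = 0.159 − 0.023 = 0.136
- True mean fall of 20%, mirror: 1 − Φ(−1) = 0.841

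| σ | μ = 0, written | μ = 0, mirror | μ = 20, written | μ = 20, mirror |
|---|---|---|---|---|
| 5% | 0.477 | 0.023 | 0.023 | 0.977 |
| 10% | 0.341 | 0.159 | 0.136 | 0.841 |
| 15% | 0.248 | 0.252 | 0.161 | 0.748 |

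At each of these SDs the written CO2 limb labels more participants improved when nothing happened than when CO2 truly fell by 20% on average. The mirror limb orders the two situations correctly. It does not remove noise: at σ = 15% about a quarter still qualify with no true change.

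Because of and/or, the probability of meeting the combined capnography criterion is at least that of meeting the CO2 limb. Each written-limb figure is therefore a floor for the combined criterion, not its response rate.

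**The case against.** The strongest reply is that this is a slip of sign convention. The neighbouring thresholds show the intent, a signed change of -10% or lower, and an evaluator is unlikely to score a 30% CO2 fall as no improvement. That may be the intent, but the text does not say so, and a stated cut-off should not need guessing. A PDF-reading fault is unlikely, since both inequality signs appear in the same parenthesis.

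A reader might go further than the text allows in three ways:

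- **That real improvement on CO2 is scored as failure.** This is not so for the combined criterion. A participant with a 20% CO2 fall still qualifies if O2 rises by at least 10%.
- **That the capnography outcome is biased towards no difference or reversed.** The ordering shown above holds for the CO2 limb under an assumed SD. For the combined criterion there are only floors, and the document gives nothing on the joint behaviour of O2 and CO2 from which to go further. Nor does the Sample size and Statistics section commit to comparing capnography responder proportions. It provides for comparing quantitative data as such, and the one categorisation it specifies, for the multiple correspondence analysis, uses quartiles rather than this cut-off.
- **That the case report form carries the same error.** No form is shown, so this is unknown.

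These limits narrow the consequence. They leave the wrongly written threshold in place.

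**Conclusion.** The CO2 limb is wrong as written. It treats 10% as a maximum fall, against the O2 limb and the other numeric perfusion thresholds, and nothing in the article corrects it. The logical point rests on the text alone. The percentages rest on an assumed normal distribution and SD and describe the CO2 limb only.

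The supported consequence is that any classification using the criterion admits participants on trivial CO2 falls and recognises large falls only through O2, so it is diluted by noise. A bias in the combined capnography outcome, or a reversal of it, is not established. The reach is one component of a secondary efficacy outcome. The primary outcomes are ulcer epithelialization and major amputation, and the sample size rests on ulcer healing rates of 75% and 30%; neither uses capnography.

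**What to change.** Before any CO2 responder is classified, reconcile the CO2 inequality with the O2 one by writing *decrease ≥ 10%*, or equivalently *change ≤ -10%*. Check that any data form carrying the threshold matches. No new analysis is needed to compare O2 and CO2 as continuous values, since the statistics section already provides for comparing quantitative data.

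The cost is one symbol, a check of the forms and, under the Ethical and regulatory considerations section, submission of the change as a protocol amendment. The sample size, visits and measurements do not change.

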**Methods:**

An open randomized clinical trial will be carried out with two groups of twenty patients with CLI: In group 1, 2g of abdominal adipose tissue will be taken to produce ASCs. These cells will then be expanded in a lab (cell processing center) for 14–21 days before being applied to the lesion using bio-dressings and perilesional subcutaneous injections. Group 2 will receive conventional treatment with hydrogel-based dressing. There will be regular clinical assessments, supplementary tests, and photo documentation. The main efficacy outcome will be partial or complete healing of the wound. Safety outcomes will be monitored for infections, gangrene, amputations, and death. Participants will be monitored for 90 days. Cases of major amputation of the studied limb will not be included. The results will be evaluated by an independent external evaluator who is blind to the groups. Considering the high prevalence and socioeconomic consequences related to CLI and limb amputation, this study is expected to provide a positive social and financial impact on the Brazilian Unified Health System.

ClinicalTrials.gov: NCT06326203.

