### Randomization

Randomization will be prepared by a technician, using a random numerical table construction program available at http://stattrek.com/Tables/Random.aspx. Twenty positions will be drawn, with number 1 being fixed for Group 1 (cell therapy) and number 2 for Group 2 (control), randomly and consecutively. The envelope containing the randomization sequence will be held by an independent professional, the study team will not have access to the allocation order until time for adipose tissue collection.

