### Adverse effects

Risks related to the use of autologous ASCs have not yet been described, considered non-existent for this study if they follow a rigorous cell production process. Treatment-related risks are those related to the surgical anesthetic procedure: surgical site infections, surgical wound dehiscence, worsening of pain in the treatment area, bleeding, gangrene, and cellulitis.

Partial data analysis will be conducted once at least five participants have been included in each group. The study will be halted if a statistically significant difference is observed in the primary or secondary safety outcomes for either group. In such a case, the Ethics and Research Committee/National Research Ethics Commission (CEP/CONEP) will be notified, and all necessary measures will be implemented.

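### Follow-up has two incompatible time origins; under one of them, Group 1's fat harvest and 14–21 day expansion wait are not counted for safety

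*Protocol article*

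**What the plan says.** All places are in the protocol article.

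- **Participant timeline, first origin:** "Follow-up of patients will continue for 120 days from the moment they receive treatment with the proposed advanced cell therapy". The section then adds: "Time required for screening and preparations will not count toward the study follow-up period".
- **Participant timeline, second origin:** "Participants will be reassessed on days 7, 30, 60, 90, and 120 days after randomization".
- **Abstract, Methods:** "In group 1, 2g of abdominal adipose tissue will be taken to produce ASCs", with 14–21 days of laboratory expansion before application. The same paragraph gives a different length of follow-up: "Participants will be monitored for 90 days".
- **Randomization:** "the study team will not have access to the allocation order until time for adipose tissue collection". The harvest therefore comes at or after the opening of allocation.
- **Group 1 and control group descriptions:** both arms have the ulcer debrided. Only Group 1 receives cells, and no harvest or expansion is described for controls.
- **Secondary outcomes, Safety:** every adverse event is covered, but no date is given from which events count. The primary safety outcome, absence of major amputation, has no stated window either.
- **Participant replacement:** a participant excluded in the screening period, which is bounded by the receipt of cell therapy, may be replaced in the same randomization position.
- **Adverse effects:** "Treatment-related risks are those related to the surgical anesthetic procedure: surgical site infections, surgical wound dehiscence, worsening of pain in the treatment area, bleeding", followed by gangrene and cellulitis.

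**The concern.** The strategy under test is harvest, expansion and application together. The first two steps follow the opening of allocation and occur in one arm only, so they are not neutral run-in time. If Group 1's clock starts at application and the controls' clock at randomization, complications of the harvest, and any death, infection or amputation during the wait, drop out of Group 1's safety results. Control events over the same period stay in.

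The replacement rule could add to this. Its stated limit is the receipt of cell therapy, so a Group 1 participant excluded during the wait might be replaced as well as left uncounted. The interim look described under Adverse effects, taken once at least five participants per group are included, compares the same safety outcomes and would inherit the same gap.

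Safety is a primary objective, and with 20 participants per arm one or two uncounted events can change the picture.

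**Working it through.** The plan gives no computed figure on this point, so the check compares the two stated origins by day arithmetic.

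**Inputs.** Follow-up of 120 days and visits on days 7, 30, 60, 90 and 120 (Participant timeline); expansion of 14–21 days (Abstract, Methods); 20 participants in Group 1 (Sample size). Assumption: randomization, opening of allocation and harvest fall on about the same day, and application follows when expansion ends.

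**Origin A, cell application (Group 1).**
- Last visit, in days from harvest: 14 + 120 = 134 to 21 + 120 = 141.
- Uncounted share: 14/134 = 10.4% to 21/141 = 14.9%.
- Uncounted time in the arm: 20 × 14 = 280 to 20 × 21 = 420 participant-days.
- Controls: no start can be defined, because they receive no cells.

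**Origin B, randomization.** Day relative to application = visit day minus 14 or 21.

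| Visit (days after randomization) | 14-day expansion | 21-day expansion |
|---|---|---|
| 7 | −7 | −14 |
| 30 | 16 | 9 |
| 60 | 46 | 39 |
| 90 | 76 | 69 |
| 120 | 106 | 99 |

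The harvest and the wait now lie inside follow-up, but only 99–106 days remain after application, not 120.

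**Can one origin be read as intended throughout?** The Intervention section brings Group 1 back for reassessment 7 days after application, when the cell dressing comes off. That matches a day-7 visit under A. Under B the day-7 visit would precede application by 7–14 days. Controls can be dated only under B. Neither origin fits the whole text, and using each where it fits gives the arms different clocks.

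**Illustration only.** The documents give no harvest complication rate. For an assumed risk p per participant, expected events are 20p and the chance of at least one is 1 − (1 − p)^20.

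| Assumed p | Expected events in 20 | Chance of at least one |
|---|---|---|
| 3% | 0.6 | 46% |
| 5% | 1 | 64% |
| 10% | 2 | 88% |
| 15% | 3 | 96% |

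These figures show how few events are at issue. They do not predict what the trial will see.

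**The case against.** The strongest reply is that nothing is settled as excluded. The sentence on preparations limits what counts toward the length of follow-up; it does not say that earlier events go unrecorded or unanalysed. The visit sentence that follows would bring the harvest and the wait inside. Any adverse event is an outcome, the analysis is by intention to treat, and the Data collection plan treats death and amputation as endpoints, not as lost data. Discontinued participants are still to be followed. The assessment schedule and full protocol are supplementary files not shown here, and they may state when adverse-event collection starts.

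Much of this stands. A reader might infer that the Participant timeline section sets a single safety window that opens after the harvest. It does not, because it gives two origins. A reader might also infer that the Adverse effects section itself lists complications of the harvest and of the wait. It names neither. It speaks of the surgical anesthetic procedure, and the only procedure described with anesthesia is the cell application. Wound dehiscence could refer to the harvest site, but that is inference. Nor do the documents establish that control events will in fact be counted from allocation; the controls' debridement at Visit 1 is not dated against it.

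What the reply does not remove is the contradiction. A missing start date alone could be left to a fuller document. Two stated rules that conflict for Group 1, one of which cannot apply to controls, are an error in the text as it stands.

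**Conclusion.** The point holds as an unreconciled time origin with a consequence for safety. Under the application-based origin, the first 14–21 days after harvest, 10–15% of the 134–141 days to the last visit, are uncounted in Group 1, while controls can be dated only from randomization. The text permits, but does not settle, a safety comparison that omits harvest and waiting-period events. If it were run that way, it would favour Group 1.

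The sizes rest on harvest falling at about the time allocation is opened and on application following directly after expansion. No size can be put on the number of events lost, because no complication rate is given. The point deserves correction before recruitment is complete, since it bears on a primary objective. It does not show that the trial will in fact leave these events out.

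**What to change.** Reconcile the Participant timeline section to one safety time origin for both groups, for example:

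> All primary and secondary safety outcomes are counted in both groups from randomization (opening of allocation), and the groups are compared over the same number of days from that origin. Group 1 events between adipose tissue collection and cell application are included in the Group 1 totals. They are also shown separately, together with any Group 1 events after the end of the common window. Participants whose allocation has been opened remain in these counts even if they are replaced.

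The equal window matters. Moving the start to allocation while leaving Group 1's end at 120 days after application would count Group 1 for 134–141 days against 120 in controls, which is 12–18% longer (134/120 = 1.12; 141/120 = 1.18), and would bias the comparison the other way.

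State the efficacy time origin separately. Non-occurrence of major amputation appears under both safety and efficacy in Primary outcomes, so say which origin applies in each use. The 90 days in the Abstract and the 120 days in Participant timeline must also be reconciled before the common window can be fixed.

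The cost is a few sentences and an extra block in the safety table. The change concerns counting, not care. There are two downsides: Group 1's safety results may look slightly less favourable, and a common window of 120 days from allocation would cover only 99–106 days after application, which is why later Group 1 events should be shown as well.

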### Intervention

In the treatment group, the active component of this project’s cell therapy product is autologous ASCs [31–33], which will be expanded in the Laboratory (Cell Processing Center). The ASC will be made available to the patient in two presentations for use in a single treatment session: injectable solution and stable bio-dressing. The dosage planned for this clinical trial will be a single application of the products.

The procedure for applying the advanced cell therapy product proposed in this clinical trial will be carried out after locoregional (preferred) or general anesthesia, at the discretion of the anesthesiologist who will accompany the procedure, considering the participant’s clinical conditions, since the procedure cannot be performed without adequate analgesia. The application of injections and dressings will follow the rules of surgical procedures, carrying out antisepsis, placement of sterile drapes, manipulation of surgical materials, and opening of envelopes containing the products to be applied in a sterile manner.

Initial surgical cleaning and debridement will be carried out on the wound to make it ready to receive the treatment. Subcutaneous applications of 0.1 mL of the product consisting of the plasma solution and expanded autologous ASC will then be carried out every 1 cm from the edge of the ulcer (in the subcutaneous layer of the intact skin at the perimeter of the lesion), so that approximately 1x10^4^ ASCs are injected by puncture.

After the injections, the topical application of the stable bio-dressing will be carried out containing the ASCs on a membrane FIBRACOL™ Plus (Systagenix Brazil, dressing containing 90% collagen and 10% calcium alginate) with the same plasma solution containing cells in the proportion of 1x10^4^ ASCs per cm^2^ of the ulcer area to be covered (Fig 2). The dressing will be covered with rayon gauze (identifying the end of the primary dressing), the secondary dressing will be composed of a thin layer of moistened gauze with 0.9% saline, a layer with dry gauze, and, finally, a crepe bandage. Only the secondary dressing will be changed daily by the participant or their caregivers, according to instructions given by the study team. After 7 days, the ASCs absorption phase will be completed and the participant will return for reassessment of the ulcer, moving on to the phase in which the dressing will contain only hydrogel.

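### Follow-up has two lengths (90 and 120 days) and two incompatible starting points (cell therapy and randomisation), so the groups are not guaranteed to be compared over the same window

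*Protocol article*

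**What the plan says.** **Length.** The abstract's Methods paragraph states "Participants will be monitored for 90 days", without saying from when. The Participant timeline section states "Follow-up of patients will continue for 120 days from the moment they receive treatment with the proposed advanced cell therapy" and places the closing assessment, numbered 6, after 120 days.

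**Origin.** The same section adds "Time required for screening and preparations will not count toward the study follow-up period", so that clock starts at cell application. It then sets the visits from a different point: "Participants will be reassessed on days 7, 30, 60, 90, and 120 days after randomization".

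**Gap between the two origins.** Under Randomization, "the study team will not have access to the allocation order until time for adipose tissue collection". According to the abstract, the cells are then expanded "for 14–21 days before being applied to the lesion". Only Group 1 has tissue taken and waits for cells.

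**First reassessment.** The Intervention section counts it from the bio-dressing: "After 7 days, the ASCs absorption phase will be completed and the participant will return for reassessment of the ulcer".

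**Control group.** The group descriptions give both groups a debridement at Visit 1, followed by the assigned care. Visit 1 is not dated relative to randomisation, and the article does not say whether the control Visit 1 waits for an expansion period.

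**Rates.** The Sample size section uses 75% and 30% healing without a day attached.

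**The concern.** Total epithelialisation and absence of major amputation are the primary outcomes, and Kaplan-Meier and Cox analyses are planned. All of these depend on when time starts and when it stops. With two lengths and two origins in the text, two people could date the same visit or count the same amputation differently, and the difference could fall along treatment lines, because only Group 1 has a wait built in.

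The direction depends on the reading. With visits dated from randomisation, Group 1 has had less time under its treatment at every nominal day. With follow-up dated from cell application, Group 2 needs a substitute for day 0, and the choice decides whether early events count alike in both groups. Without a day attached to 75% and 30%, the sample size cannot show which reading was intended.

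**Working it through.** **1. The plan's own figure.** Inputs from Sample size: p1 = 0.75, p2 = 0.30, two-sided 5%, 80% power.

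n = [1.960·√(2·p̄·(1−p̄)) + 0.842·√(p1(1−p1) + p2(1−p2))]² / (p1−p2)², with p̄ = 0.525

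= [1.960·√0.49875 + 0.842·√0.3975]² / 0.45² = (1.384 + 0.531)² / 0.2025 ≈ 18.1, so 19 per group.

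The stated 20 is consistent with this. At 20 per group, power is 84% by the same approximation and 73% by exact Fisher. This calculation contains no day, so it does not settle the clock.

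**2. Day arithmetic.** The lag from tissue collection to application is 14–21 days (abstract). Randomisation is taken as the opening of allocation at tissue collection.

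| Quantity | Lag 14 | Lag 21 |
|---|---|---|
| Day-7 visit relative to application (7 − lag) | 7 days before | 14 days before |
| Day 90 from randomisation, in days since application (90 − lag) | 76 | 69 |
| Day 120 from randomisation, in days since application (120 − lag) | 106 | 99 |
| 120 days after application, in days since randomisation (120 + lag) | 134 | 141 |

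The section on suspension of intervention tolerates up to a further month before the procedure. Taking that as 30 days (assumption), the longest lag is 21 + 30 = 51 days, and day 120 from randomisation is then day 69 after application.

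**3. The mixed reading.** If Group 1 were clocked from application and Group 2 from randomisation, the uncounted share of Group 1's time since randomisation would be 14/134 = 10% to 21/141 = 15%. No section states this combination.

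**4. Illustration of what the clock does to the expected rates.** Assumptions that are not in the article: the healing hazard is constant, 75% and 30% refer to 120 days of treatment, controls are treated at once, and no Group 1 ulcer heals before application.

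Group 1 healed at day 120 from randomisation = 1 − 0.25^((120 − lag)/120)

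- Lag 14: 1 − 0.25^(106/120) = 70.6%
- Lag 21: 1 − 0.25^(99/120) = 68.1%

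| Group 1 v Group 2 | Power, approximation | Power, exact Fisher |
|---|---|---|
| 75% v 30% | 84% | 73% |
| 70.6% v 30% | 75% | 62% |
| 68.1% v 30% | 69% | 55% |

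If Group 1 instead heals at the control rate while waiting, the rate is 1 − 0.25^((120 − lag)/120)·0.70^(lag/120), which gives 72% (lag 14) and 70% (lag 21). The loss is smaller but of the same order.

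**5. 90 instead of 120 days, with no lag.** 1 − 0.25^(90/120) = 64.6% and 1 − 0.70^(90/120) = 23.5%. Power is 77% by the approximation and 65% by Fisher.

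**The case against.** Several arguments on the other side are sound.

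- **Equal windows are available on one reading.** If visits run from randomisation, as the timeline says, both groups are seen at the same time since randomisation. That is the usual intention-to-treat comparison. A reader might infer that the groups are necessarily compared over unequal time, and the text does not support that.
- **Immortal time is not established.** A reader might infer that Group 1 events during expansion are dropped while Group 2 events count. That needs Group 1 clocked from application and Group 2 from randomisation, which no section states. The exclusion of screening and preparation time is not limited to Group 1. The article also specifies intention to treat and treats death and amputation as endpoints.
- **There are not three clocks.** The 90 days has no stated origin. It is a conflicting length, and it may be a stale figure in the abstract, since the Methods body gives 120 days consistently.
- **A shared treatment anchor is plausible.** Both groups have a Visit 1 with debridement, and Visit 1 plus five reassessments makes six. The Intervention section's 7-day return describes removal of the Group 1 dressing and does not by itself define a between-group visit.
- **The power figures belong to the randomisation clock, which is the one recommended below.** They are a cost of that choice and do not argue against it.
- **The assessment schedule, the full protocol and the SPIRIT figure are not shown** and may define day 0 by group.

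What remains is the conflict in the current text. Cell therapy and randomisation cannot fall on the same day in Group 1. Group 2 has no stated start on the treatment clock. A supplementary schedule could show the intention, but it cannot make the abstract and the timeline agree.

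**Conclusion.** The article contradicts itself on how long follow-up lasts and on when it starts. The firm part is day arithmetic on the article's own figures: a gap of 14–21 days between the two origins in Group 1, a day-7 visit 7–14 days before application, and day 120 falling at day 99–106 after application. It assumes only that randomisation means the opening of allocation at tissue collection.

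The consequence is conditional. Comparison over the same window is not guaranteed, but bias is not shown. The drop in expected Group 1 healing to about 68–71% rests on a constant hazard, no healing before application, immediate treatment of controls, and 75% meaning 120 days after application. The article states none of these, so the figure shows what depends on the choice and does not estimate a loss.

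**What to change.** 1. Reconcile the abstract, the Intervention section and the Participant timeline to one final assessment day and one day 0, defined identically for both groups.
2. Use randomisation as that day 0 for every between-group comparison (healing, amputation, death, Kaplan-Meier, Cox), and count events from it in both groups, including events in Group 1 during expansion. It is the origin consistent with the stated intention-to-treat analysis.
3. Keep the post-application checks in Group 1 as additional visits, outside the between-group comparison.
4. State when the control Visit 1 takes place relative to randomisation.
5. State that 75% and 30% refer to the chosen final day, and recheck the power against it.

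The work is amendment wording and visit-window programming. The real cost is that Group 1 has 14–21 fewer days since application at the final visit. If 75% was meant as 120 days after application, the expected difference at day 120 after randomisation is smaller than planned, and 20 per group may no longer give 80% power. The change is simplest before any control visits are dated, because inconsistent dates are hard to repair afterwards.
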